## Data analysis

4

### Statistical analysis sets

4.1

Full Analysis Set (Intention-to-Treat): All randomized participants will be included in the full analysis set and analyzed based on their initial randomized group assignment, irrespective of their compliance with the full intervention protocol. This set will constitute the primary population for the efficacy analysis.

Per-Protocol Set: This set will consist of participants who complete at least 80% of the planned treatment sessions (i.e., at least 13 sessions over the 12-week period) and have no major protocol deviations. It will be utilized for supportive sensitivity analyses.

Safety Analysis Set: This set shall encompass all participants who undergo at least one session of warm acupuncture and will be employed for the safety assessment of the intervention.

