**Figure 1 fig1:**
[figure not shown]
Flow diagram of this study. A total of 84 participants will be included in this study and will be randomized (1:1) to two groups: (1) A standard care group with only typical protective guidelines and (2) a warm acupuncture group with the same standard care and a 12-week warm acupuncture regimen. All participants will complete the 12-week intervention and a subsequent one-year follow-up.

**Table 1 tab1:** Schedule of enrolment, interventions, and assessments.

Study Schedule	Study period								
	Baseline	Discharge				Follow-up			
Timepoint	T0	T1	T2	T3	T4	T5	T6	T7	T8
Week	0	2	4	8	12	16	24	36	60
Enrollment									
Eligibility screen	**×**								
Informed consent	**×**								
Demographics	**×**								
Medical history	**×**								
Physical examination	**×**								
Laboratory examination	**×**								
CT/MRI	**×**								
ECG	**×**								
Neurological evaluation	**×**								
Interventions									
Standard care group		3 months of treatment							
Warm acupuncture group		3 months of treatment							
Assessment									
NCI-CTCAE V4.0	**×**	**×**	**×**	**×**	**×**	**×**	**×**	**×**	**×**
EORTC QLQ-CIPN20	**×**	**×**	**×**	**×**	**×**	**×**	**×**	**×**	**×**
EORTC QLQ-C30	**×**	**×**	**×**	**×**	**×**	**×**	**×**	**×**	**×**

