### Sample size calculation

2.4

This study employs a randomized controlled trial methodology to assess the effectiveness of warm acupuncture for alleviating peripheral neuropathy caused by oxaliplatin, comparing a warm acupuncture cohort with a standard care cohort. The main measure of interest is the neurotoxicity level, which will be evaluated using the NCI-CTCAE version 4.0 criteria. Based on previous research, a treatment response is indicated by a decrease of one or more grades in neurotoxicity (37). The expected response rates for the two groups are 0.8 and 0.47, respectively. Utilizing a standard formula for the comparison of two proportions, with a two-tailed alpha level of 0.05 and a power of 80% (*β* = 0.2), a minimum of 33 participants is necessary for each group. Considering an estimated dropout rate of approximately 20%, the target sample size is established at no less than 40 participants per group. Consequently, the overall sample size for this investigation is set at 84 participants, with 42 in each group.

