#### Safety assessment

3.3.3

The evaluation of adverse events will be conducted using the NCI-CTCAE version 4.0, released on June 14, 2010. This terminology serves as a framework for reporting adverse events. Following each treatment session, an additional safety assessment will be performed to record any side effects experienced by participants in both treatment groups.

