Additional statistical details are predefined. In the primary models, we will adjust for key baseline covariates that display an imbalance (*p* < 0.1) or possess established prognostic significance (e.g., number of chemotherapy cycles). If a significant group-by-time interaction is identified, Bonferroni-corrected *post hoc* pairwise comparisons will be conducted. Missing data, assumed to be missing at random, will be managed using the likelihood-based estimation inherent to linear mixed models; the robustness of findings will be assessed through sensitivity analyses, including the last observation carried forward method. All adverse events will be summarized using descriptive statistics, and between-group differences in incidence rates will be evaluated using the Chi-square test or Fisher’s exact test, as appropriate. For participants who withdraw from the study, the primary efficacy analysis will follow the Intention-to-Treat (ITT) principle, with linear mixed models handling missing data under the Missing at Random assumption. A Per-Protocol (PP) analysis will be conducted as a sensitivity measure. All withdrawals and protocol deviations will be recorded with detailed reasons.

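### The Safety Analysis Set is limited to participants who had warm acupuncture, so the planned between-group adverse event tests have no standard care comparator

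*Protocol article*

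**What the plan says.** The protocol article defines three analysis sets under Statistical analysis sets (4.1). The full analysis set holds all randomised participants and is the primary population for efficacy. The per-protocol set serves supportive sensitivity analyses. The safety set is defined by exposure to the experimental treatment: "This set shall encompass all participants who undergo at least one session of warm acupuncture". The same sentence gives its purpose: it "will be employed for the safety assessment of the intervention". No other population is named for safety.

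Three other places bear on the point.

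- **Content of the control arm.** The Figure 1 legend describes it as "A standard care group with only typical protective guidelines". Standard care group (3.1) lists five protective instructions and no sessions of any kind.
- **Collection of adverse events.** Safety assessment (3.3.3) says: "Following each treatment session, an additional safety assessment will be performed". In the same sentence, the stated purpose is to "record any side effects experienced by participants in both treatment groups".
- **Analysis of adverse events.** Statistical methods (4.2) says that, beyond descriptive summaries, "between-group differences in incidence rates will be evaluated using the Chi-square test or Fisher’s exact test, as appropriate". It does not name the analysis set for these tests.

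**The concern.** A between-group test needs participants in both groups. The only population that the article assigns to safety admits people through an exposure that one arm never has. Followed literally, the plan collects events in both arms and then removes one arm before comparing them.

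The abstract gives safety equal standing with effectiveness in the trial's aim, and this test is the only inferential safety analysis described. If the definition stays as it is, someone will have to choose a different safety population once data exist, in a trial where patients and practitioners know the allocation. A fixed definition avoids that choice.

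A second, smaller matter follows from the wording of 3.3.3. The additional safety assessment is attached to treatment sessions, which only the acupuncture arm has, yet the sentence says it covers both arms. Adding controls to the safety set does not settle how they are assessed.

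**Working it through.** **Inputs from the protocol article**

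- Arm sizes (2.4): "the overall sample size for this investigation is set at 84 participants, with 42 in each group".
- Expected response rates 0.80 and 0.47, two-sided alpha 0.05, power 80%, 33 evaluable per group, dropout about 20% (2.4).
- Acupuncture sessions (3.2): twice weekly for weeks 1 to 4 and once weekly for weeks 5 to 12, so 2 × 4 + 1 × 8 = 16. Standard care sessions (3.1): none.

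**Step 1. Confirm the arm sizes.** The usual two-proportion formula with pooled variance under the null is

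n = [z(0.975)·√(2·p̄·(1−p̄)) + z(0.80)·√(p₁(1−p₁) + p₂(1−p₂))]² / (p₁−p₂)², with p̄ = (0.80 + 0.47)/2 = 0.635.

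This gives [1.960 × √0.46355 + 0.842 × √0.4091]² / 0.33² = 32.2, rounded up to 33 per group, as the article states. Allowing for dropout, 33/(1 − 0.20) = 41.25, so 42 per group and 84 in total. The arm sizes reproduce. They serve here only as denominators.

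**Step 2. Count the safety set by arm, with participants treated as allocated.**

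| | Randomised | In the safety set as written | In a set of all randomised participants, by treatment received |
|---|---|---|---|
| Warm acupuncture | 42 | up to 42 | up to 42 |
| Standard care | 42 | 0 | 42 |

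In the last column, anyone randomised to acupuncture who never has a session counts under standard care, so the total stays at 84.

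**Step 3. Apply the planned tests to the set as written.** Let a of 42 acupuncture participants have an event. The control row is (0, 0).

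- Chi-square: the expected counts in the control row are 0 × a/42 = 0 and 0 × (42 − a)/42 = 0. The statistic divides by these and is undefined.
- Fisher: with a row total of zero, only one table fits the margins. Its probability is 1, so p = 1 for every a, and the odds ratio is undefined.

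With an assumed 6 events in 42, purely for illustration, the table [6, 36; 0, 0] gave Fisher p = 1.0 and no odds ratio, and the Chi-square routine stopped on a zero expected count.

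**Step 4. Apply the same test with controls included.** The assumed 6/42 against an assumed 0/42 gives Fisher p = 0.026. These event counts come from no document. They show only that the test can respond to data once the comparator is present.

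**Step 5. Read the 3.3.3 sentence against the interventions.** The assessment follows each treatment session. Section 3.2 gives one arm 16 sessions, and section 3.1 gives the other none. The sentence nevertheless names both arms. Either controls have equivalent contacts that the article does not describe, or the additional assessment reaches one arm only. The text does not say which.

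**The case against.** The strongest defence is that 4.2 does not name the population for the adverse event tests, and that 4.1 could mean only that harms of the intervention are described among those exposed to it. Control data are clearly intended: 3.3.3 refers to both arms, Outcomes (3.3) records any adverse events, and Data collection and monitoring (2.6) provides continuing safety monitoring through the electronic data capture system. The comparison can therefore be recovered by correcting a definition, with no loss of data. This stands as a limit on the consequence. It does not remove the contradiction: on the narrow reading the between-group test has no defined population at all, and on the natural reading its population has no controls. A control who crossed over to acupuncture would enter the set, but would not be an untreated comparator.

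A reader might go further and infer that the acupuncture arm will be questioned up to 16 more times than controls, and that this inflates its apparent event rate by a calculable amount. The documents do not support that. The additional assessment is said to cover both arms, so unequal questioning is a plausible risk and not a documented plan. How controls are asked about events is detail that an article may leave to the full protocol. Any figure for the inflation would need a detection probability per contact, an assumption about recall between contacts, and knowledge of whether the week 2, 4, 8 and 12 visits coincide with sessions. The article gives none of these. With full recall, the number of contacts over the same 12 weeks would not change cumulative incidence.

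It may also be tempting to restrict the test to events elicited at the common visits. That would drop session-recorded and spontaneously reported events from the comparison, and Table 1 has no adverse event row at those visits.

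**Conclusion.** The contradiction stands. As written, the only population named for safety contains 0 of 42 controls and up to 42 acupuncture participants, while the plan records events in both arms and tests the difference between them. This result assumes only that participants are treated as allocated, and that the set which 4.1 assigns to safety is the one used for the tests in 4.2. It rests on what the article states, so it is not a gap that an unseen analysis plan could be expected to fill.

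The error lies in the definition. The article does not say that control events go uncollected, and a reader should not infer it. On ascertainment, the supportable conclusion is limited to a sentence in 3.3.3 that needs reconciling and a possible imbalance that reporting should make visible. No size is claimed for it. The sample size and the primary efficacy analysis are unaffected.

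**What to change.** 1. In 4.1, redefine the Safety Analysis Set as all randomised participants, grouped by treatment received: at least one warm acupuncture session counts as warm acupuncture, otherwise standard care.
2. In 4.2, name this set as the population for the Chi-square or Fisher comparison of adverse event incidence.
3. In 3.3.3, reconcile the session-linked additional assessment with the statement that it covers both arms, by saying how it applies to participants who have no sessions.
4. Keep all recorded events in the overall comparison. Alongside it, report separately those first recorded at session-only contacts, so that a reader can see how much of any difference arises there.

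The cost is one definition, a sentence each in 4.2 and 3.3.3, and a field on the adverse event form that marks whether an event was first recorded at a session-only contact. The sample size, treatment schedule and efficacy analysis do not change.

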### Statistical methods

4.2

Analysis of Baseline Characteristics: The baseline characteristics of each group will be delineated using appropriate summary statistics. For normally distributed continuous variables, the results will be shown as means ± standard deviations, with independent sample t-tests utilized for comparisons between groups. If the distribution is not normal, these variables will be reported as medians (interquartile ranges) and analyzed using the Mann–Whitney U test. Categorical data will be reported as frequencies (percentages) and analyzed for differences between groups using either the Chi-square test or Fisher’s exact test, depending on the situation.

Analysis of the Primary Outcome: The primary focus will be on the ordinal categorical variable representing the neurotoxicity grade according to NCI-CTCAE version 4.0. A Generalized Estimating Equations (GEE) approach or a mixed-effects ordinal logistic regression model will be utilized to analyse the primary outcome. This model will be used to conduct a statistical assessment comparing the effectiveness of warm acupuncture with alternative treatments, emphasizing differences between groups, temporal effects, and their interactions to determine its role in reducing neurotoxicity.

Analysis of the Secondary Outcomes: Secondary outcomes, which include the continuously measured scores from the EORTC QLQ-CIPN20 and the commonly used EORTC QLQ-C30 scales, will be analyzed using a linear mixed-effects model. This model will incorporate fixed effects for group, time, visit, and the interaction between group and time, while subject will be treated as a random effect. This approach aims to assess the variations in symptom burden and quality of life across groups and their changes over time.

Additional statistical details are predefined. In the primary models, we will adjust for key baseline covariates that display an imbalance (*p* < 0.1) or possess established prognostic significance (e.g., number of chemotherapy cycles). If a significant group-by-time interaction is identified, Bonferroni-corrected *post hoc* pairwise comparisons will be conducted. Missing data, assumed to be missing at random, will be managed using the likelihood-based estimation inherent to linear mixed models; the robustness of findings will be assessed through sensitivity analyses, including the last observation carried forward method. All adverse events will be summarized using descriptive statistics, and between-group differences in incidence rates will be evaluated using the Chi-square test or Fisher’s exact test, as appropriate. For participants who withdraw from the study, the primary efficacy analysis will follow the Intention-to-Treat (ITT) principle, with linear mixed models handling missing data under the Missing at Random assumption. A Per-Protocol (PP) analysis will be conducted as a sensitivity measure. All withdrawals and protocol deviations will be recorded with detailed reasons.

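### The 80% power is calculated for a responder comparison that section 4.2 does not plan; no visit or model term is named as the primary test, so the power is not shown for any planned analysis

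*Protocol article*

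**What the plan says.** **Sizing (protocol article, section 2.4).** The endpoint is binary: "a treatment response is indicated by a decrease of one or more grades in neurotoxicity". "The expected response rates for the two groups are 0.8 and 0.47, respectively". The method is given as "Utilizing a standard formula for the comparison of two proportions", two-sided alpha 0.05 and 80% power, and the result is that "a minimum of 33 participants is necessary for each group". Allowing for about 20% dropout, the trial is set at 42 per group, 84 in total. No visit is given at which response is read.

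**Primary outcome (sections 3.3 and 3.3.1).** This is the CTCAE version 4.0 neurotoxicity grade. It has no responder definition and no primary visit. Table 1 lists nine assessments, T0 to T8 (weeks 0, 2, 4, 8, 12, 16, 24, 36 and 60), none marked as primary. The text of 3.3 does not list a separate end-of-treatment visit at week 12, so it supplies no default either.

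**Primary analysis (section 4.2).** The ordinal grade is analysed by GEE or by a mixed-effects ordinal logistic model, "emphasizing differences between groups, temporal effects, and their interactions to determine its role in reducing neurotoxicity". The later paragraph adds: "If a significant group-by-time interaction is identified, Bonferroni-corrected" post hoc pairwise comparisons follow. The number of comparisons is not given. Chi-square and Fisher tests appear only for baseline characteristics and adverse events.

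**The concern.** A power statement is useful only if it belongs to the test that decides the trial. Here the sized test (two proportions, one unstated visit) and the planned analysis (ordinal grade, all visits, three kinds of effect) differ in variable, time and hypothesis.

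The article also leaves open which result would count as the primary one: the group effect, the group-by-time interaction, or a contrast at one visit. These answer different questions and can disagree on the same data. The interaction asks whether the group difference changes over time. It does not say when, or in whose favour.

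Making visit contrasts conditional on that interaction has a perverse result if the model covers post-baseline visits only. A benefit that appears at week 2 and holds steady produces no interaction, so the visit contrasts would rarely be reached in the case most favourable to the treatment.

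**Working it through.** **1. Reproduce the stated sample size.** Inputs from section 2.4: p1 = 0.80, p2 = 0.47, d = 0.33, two-sided alpha 0.05, power 80%. The mean proportion is 0.635.

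n = [z(0.975)·√(2·0.635·0.365) + z(0.80)·√(0.80·0.20 + 0.47·0.53)]² / d²
= [1.960·0.6808 + 0.8416·0.6396]² / 0.1089 = 32.2, rounded up to 33.

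Dropout: 33/0.8 = 41.25, rounded up to 42 per group, 84 in total. The stated figures reproduce (pooled variance, no continuity correction).

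**2. Power of the sized test.** Power = Φ{[d√n − z·0.6808]/0.6396}.

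- n = 33, alpha 0.05: (1.896 − 1.334)/0.6396 = 0.878, so 81.0%.
- n = 42, alpha 0.05: (2.139 − 1.334)/0.6396 = 1.257, so 89.6%.
- If the same contrast were Bonferroni-corrected over the 8 post-baseline visits (alpha 0.00625, z = 2.734): 52.1% at n = 33 and 66.7% at n = 42. The divisor of 8 is an assumption.

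**3. Power of the visit-averaged group effect (illustration).** The article gives no grade distribution, within-patient correlation or time course, so these are assumed. Take 33 per arm, a continuous approximation with compound symmetry, correlation ρ = 0.5 or 0.7, no baseline adjustment, and an effect with exactly 80% power at week 12 (noncentrality 1.960 + 0.842 = 2.802). With K visits in the average and f the mean effect as a fraction of the week-12 effect:

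noncentrality = 2.802·f / √{[1 + (K − 1)ρ]/K}.

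Example, constant benefit from week 2, eight post-baseline visits, ρ = 0.5: f = 1, divisor √0.5625 = 0.75, noncentrality 3.735, power 96%.

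| Time course | T0 as outcome row (K = 9), ρ 0.5 / 0.7 | Post-baseline only (K = 8), ρ 0.5 / 0.7 |
|---|---|---|
| Constant from week 2 | 92% / 83% | 96% / 90% |
| Linear rise to week 12, then held | 73% / 61% | 82% / 71% |
| Linear rise to week 12, zero by week 60 | 44% / 35% | 53% / 42% |
| Linear rise to week 12, zero by week 36 | 31% / 25% | 37% / 30% |

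A separate simulation on the responder scale (33 per arm, post-baseline visits only, latent correlation 0.5 or 0.8, 4000 runs) gave 95–99% for a constant effect, 80–94% for a rise then held, and 53–68% for a rise then waning to zero by week 60.

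**4. The interaction gate.** In that simulation the 7-df interaction was significant in about 4% of runs under a constant post-baseline benefit, which is its null. It was significant in 46–55% when benefit rose and held, and in 54–65% when it rose and waned. If T0 is instead an outcome row, a constant benefit is itself an interaction. Under the assumptions of step 3 the noncentrality is then 2.802²·(8/9)/(1 − ρ), which is 14.0 or 23.3 on 8 df, giving roughly 76% or 95% power. So the behaviour of the gate depends on a modelling choice that the article does not state.

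**The case against.** The best defence has three parts.

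- **Dichotomised sizing is common.** Sizing on a dichotomised form of the same scale and then analysing the ordinal scale is a familiar simplification, and a repeated ordinal analysis can be more efficient than one binary comparison. This is right, and step 3 shows power above 80% in several scenarios.
- **The SAP may settle it.** Baseline handling, the coding of time and the exact contrast commonly sit in an SAP, which is not shown. Those details are not held against the article. But the article itself states the sizing endpoint and the primary analysis, and the two do not match.
- **The design is meant to be longitudinal.** The Discussion says the trial is to look at both immediate and long-term effects, so week 12 is not the only defensible visit. That stands; it is offered below as an example.

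A reader might also infer more than the text supports.

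- *The trial is underpowered.* The low figures in the table need a benefit that builds slowly or wanes, most of them lower still with T0 averaged in as an outcome. The article states none of this.
- *Visit contrasts have only 52% power.* That figure assumes 8 comparisons and applies a two-proportion test. The planned contrasts come from a covariate-adjusted ordinal model and are labelled post hoc.
- *Type I error is 9.75%.* The sum 1 − 0.95² supposes that success would be claimed on either of two independent terms. No section says so.

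**Conclusion.** The concern holds as a mismatch between two stated parts of the article, together with the absence of a named primary test. The 33 and 84 are computed correctly, and 81% power at 33 per arm is right for a single responder comparison. That comparison is not in section 4.2, and 80% power is not shown for anything that is.

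No single power figure can be put on the planned analysis. The span of about 25% to 96% for the visit-averaged group effect rests on compound symmetry, ρ of 0.5 to 0.7, 33 per arm and the assumed time courses. It shows how much turns on unstated choices. It is not an estimate of this trial's power, and it does not establish a shortfall. The statement that the gate would rarely open holds for a constant benefit modelled over post-baseline visits, not when T0 is an outcome row.

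The point should be settled, because the primary conclusion otherwise depends on a choice of model, term and visit that is still open.

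**What to change.** Name one primary test, in the same words, in sections 2.4, 3.3.1 and 4.2. Do this before any unblinded comparison is seen. Waiting until database lock is too late, because section 2.6 lets the data monitoring committee request unblinding at interim evaluations.

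**Simplest option.** Make the primary test the between-group difference in response, a drop of at least one grade from T0, at one named visit, for example T4 (week 12, end of treatment), two-sided 0.05, not gated on the interaction. The 33 evaluable and 84 in total then stand, with 81% power. Name the test as well: 81% belongs to the uncorrected pooled comparison, while Fisher's exact test has 74.8% at 33 per arm and 85.8% at 42. The ordinal model over all visits, with T0 grade as a covariate, becomes supportive.

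**Alternative.** If the ordinal model stays primary, name one ungated contrast at one visit, restate its power with the assumed grade distribution and within-patient correlation, and make the responder difference the first supporting analysis.

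**Cost.** The first option is a change of wording, with no extra patients or data. The other visits become supportive, and dichotomising the grade loses some information. The second keeps that information but needs a new power calculation, which may not return 84.

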### Study design

2.1

This clinical trial is designed as a randomized, controlled study with the assessors blinded to the treatment allocation. It will be conducted in six medical facilities throughout China, including the Jiangsu Province Hospital with Integration of Chinese and Western Medicine, Huai’an Hospital of Traditional Chinese Medicine, Yancheng Hospital of Traditional Chinese Medicine, Jiangyin Hospital of Traditional Chinese Medicine, Dongtai Hospital of Chinese Medicine, and Nanjing Lishui District Hospital of Traditional Chinese Medicine. The recruitment of participants will occur simultaneously in outpatient settings and hospital wards.

The Institutional Ethics Committee at the coordinating centre has reviewed and granted approval for this study, as indicated by the approval number 2024-LWKYZ-008, which remains valid until February 23, 2027. Prior to participation, all individuals will provide written informed consent. Participants who are enrolled will receive complimentary warm acupuncture treatment. The methodology in this trial is meticulously organized, ensuring that ethical standards are met. The protocol aligns with the Standard Protocol Items: Recommendations for Interventional Trials (SPIRIT) guidelines to uphold scientific integrity (35). Additionally, the results will be reported in accordance with the relevant Consolidated Standards of Reporting Trials (CONSORT) extension guidelines, ensuring rigorous quality control throughout the research (36).

Participants who meet the criteria will be randomly divided into two groups, with an equal ratio of 1:1, assigning them to either the warm acupuncture group or the standard care group. All individuals will participate in a treatment phase lasting 12 weeks, followed by a follow-up period of 1 year. Medical statisticians will analyse the outcome data. This trial has been officially registered with the Chinese Clinical Trial Registry (Registration number: ChiCTR2400082506). The flow of this study is illustrated in Figure 1, while a comprehensive schedule for enrolment, interventions, and assessments is provided in Table 1.

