### Warm acupuncture group

3.2

Alongside standard care, patients will receive warm acupuncture therapy. They will lie on their backs with the treatment areas properly exposed and sanitized. Acupuncture will be applied to the following specific points: Quchi (LI11), Waiguan (TE5), Hegu (LI4), and Baxie (EX-UE9) on the arms; Guanyuan (CV4) on the abdomen; and Zusanli (ST36), Sanyinjiao (SP6), Taichong (LR3), and Bafeng (EX-LE10) on the legs. A qualified practitioner with 3 years of experience will perform needling using single-use stainless steel needles (0.25 mm × 40 mm, sourced from Suzhou Hualun Medical Apparatus Co., Ltd., China). The insertion depth and angle will follow the guidelines in The Science of Acupuncture, utilizing a consistent reinforcing–reducing technique to prioritize patient safety and treatment efficacy. Once the deqi sensation is achieved, a 27-mm moxa stick (from Nanyang Baicaotang Natural Moxa Products Co., Ltd., made from 10-year aged moxa, measuring 18 mm × 27 mm) will be placed on the needle handles at Zusanli (ST36) and Guanyuan (CV4). The moxa stick will be held approximately 20 mm above the skin, separated by a small paper sheet. The base of the moxa stick will be ignited and allowed to burn out completely, after which the paper will be removed while the moxa remains on the needle. The needles will generally remain in place for 20 to 30 min before the ash is cleared and the needles are removed. This treatment will occur twice weekly during the first 4 weeks and once weekly from weeks five to 12, with each session lasting 30 min, completing a full 12-week course. This tapered frequency schedule was designed to achieve rapid symptom control during the initial intensive phase and to consolidate therapeutic effects during the subsequent maintenance phase.

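### The secondary-outcome model lists both time and visit with only a group-by-time interaction: redundant if time is categorical, a forced straight-line group effect if time is continuous

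*Protocol article*

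**What the plan says.** Section 4.2 states that the QLQ-CIPN20 and QLQ-C30 scores "will be analyzed using a linear mixed-effects model". It then fixes the terms: "This model will incorporate fixed effects for group, time, visit, and the interaction between group and time". The only random term named is the one for subject. There is no group-by-visit term and no spline, polynomial or piecewise term.

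Three other places bear on how time could be coded:

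- Table 1 gives one time axis: "Week 0 2 4 8 12 16 24 36 60", labelled T0 to T8.
- Section 2.1: "All individuals will participate in a treatment phase lasting 12 weeks, followed by a follow-up period of 1 year". Section 3.2: "This treatment will occur twice weekly during the first 4 weeks and once weekly from weeks five to 12". Treatment therefore ends at week 12 and observation continues to week 60.
- Later in section 4.2: "If a significant group-by-time interaction is identified, Bonferroni-corrected" pairwise comparisons follow.

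**The concern.** All scores are collected at scheduled visits, so time and visit describe the same thing unless the plan defines them differently, and it does not. The sentence can be read in ways that lead to different analyses, and only some of these give a separate group difference at each visit.

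The discussion (section 5) says the design is meant to show both the immediate and the long-term effect. A single slope from week 0 to week 60 cannot separate the two when treatment is more frequent for 4 weeks, weekly to week 12 and then stops. This is not a detail left out for a later document: the article itself fixes the list of terms.

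**Working it through.** The plan gives no figure for this model, so there is none to reproduce. The inputs are the term list in section 4.2, the nine weeks in Table 1, two groups, and 42 patients per group (section 2.4).

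**Step 1. What each coding can estimate.** Two groups at nine visits give 2 × 9 = 18 cell means, so no coding in which time is the visit schedule can have rank above 18.

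| Time | Visit | Columns | Rank | Group effect |
|---|---|---|---|---|
| categorical | categorical | 1+1+8+8+8 = 26 | 18 | free at each visit |
| categorical | numeric index | 1+1+8+1+8 = 19 | 18 | free at each visit |
| phase (baseline, treatment, follow-up) | categorical | 1+1+2+8+2 = 14 | 12 | one value per phase |
| continuous, nominal week | categorical | 1+1+1+8+1 = 12 | 11 | straight line |
| continuous, nominal week | numeric index | 5 | 5 | straight line |
| continuous, actual elapsed time (jitter SD 0.5 week, assumed) | categorical | 12 | 12 | straight line |

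In the first row the eight visit columns repeat the eight time columns. Setting this design beside the model with group, one categorical time factor and their interaction (18 columns, rank 18) leaves the joint rank at 18. The two therefore span the same space, and the group-by-time contrasts are identical once the aliased columns are dropped.

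In the fourth row the two problems occur together: the time main effect is aliased with visit, and the group difference is still a straight line.

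**Step 2. Size of the distortion, continuous time only.** The modelled group difference at week w is a + b·w. With complete data and a random subject intercept, generalised least squares on the nine visits equals ordinary least squares; intraclass correlations of 0.3, 0.5 and 0.7 gave the same fits.

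- Mean week = (0+2+4+8+12+16+24+36+60)/9 = 162/9 = 18.
- Sum of squares about the mean = 5956 − 9 × 18² = 3040.
- Week 60 alone contributes (60 − 18)² = 1764, and 1764/3040 = 58%.

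The documents give no expected course for either score, so the true difference is assumed to rise linearly from 0 to 1 at week 12.

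*Sustained at 1 after week 12.* The nine values sum to 6.167 (mean 0.685) and Σ w·d = 155.

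- b = (155 − 18 × 6.167)/3040 = 44/3040 = 0.0145 per week; a = 0.685 − 18b = 0.425.
- Week 12: 0.60 (true 1). Week 60: 1.29 (true 1).

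*Linear loss to 0 at week 36.* The values sum to 3.5 (mean 0.389) and Σ w·d = 44.33.

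- b = (44.33 − 63)/3040 = −0.0061 per week; a = 0.389 − 18b = 0.499.
- Week 12: 0.43 (true 1). Week 60: 0.13 (true 0).

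Range over assumed courses:

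| Course after week 12 | Fit at week 0 (true 0) | Fit at week 12 (true 1) | Fit at week 60 (true) |
|---|---|---|---|
| sustained | 0.42 | 0.60 | 1.29 (1) |
| half lost by week 60 | 0.48 | 0.55 | 0.83 (0.5) |
| lost by week 60 | 0.53 | 0.50 | 0.37 (0) |
| lost by week 36 | 0.50 | 0.43 | 0.13 (0) |
| lost by week 24 | 0.44 | 0.36 | 0.02 (0) |

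**Step 3. Effect on the follow-on tests, continuous time only.** If the effect is lost by week 60, the fitted slope is −0.0027 per week, a change of 60 × 0.0027 = 0.16 over the study against a true peak of 1. An interaction test of that slope could miss a real week-12 difference.

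**The case against.** The strongest reply is that the article itself points to categorical time. Pairwise comparisons after a group-by-time interaction make sense when time has discrete levels, whereas a single slope difference leaves nothing to compare pairwise. Table 1 also lists discrete timepoints, and nothing in section 4.2 calls time linear or continuous; there, continuous measurement describes the scores. On that reading the extra term does no harm.

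This largely stands. A reader might infer that the model is not estimable, or that it cannot give an unbiased group difference at week 12 or in follow-up. The documents do not support either: with categorical time only the duplicate main-effect columns are aliased, and every group-by-time contrast remains available. Nor should the negative slope in the week-36 scenario be called simply the wrong sign. It is wrong for weeks 0 to 12 and right for the decline that follows.

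The reply does not fully settle the matter. The text never says that time is categorical, and the sentence on pairwise comparisons follows one about the primary models, so it could be read as covering those only. The continuous reading therefore remains open.

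**Conclusion.** The term list is a specification error that should be corrected. On the better-supported reading (categorical time) it is a redundancy with no effect on the results. On the less-supported reading (continuous time) the week-12 difference is understated, with fits of about 60% of the truth for a sustained effect and 43% for one gone by week 36 (60% to 36% over the courses tried), and a difference appears at baseline where none exists. Those figures rest on assumed effect curves, complete data and a random subject intercept. They are illustrations, not predictions. The primary ordinal analysis and the sample size are not touched.

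**What to change.** Replace the term list in section 4.2 with one time factor: group, categorical visit and group-by-visit, with subject random as now. Use the eight post-baseline visits (T1 to T8) as the response, and adjust for the T0 score and for centre, which is the randomization stratum in section 2.5. Name the week-12 group difference as the lead contrast and present the later visits as durability.

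This takes a sentence or two. The model has 2 × 8 = 16 group-by-visit means plus 1 + 5 = 6 covariate terms (T0 score, six centres), a few more parameters than a straight-line model and so some loss of precision. The covariance structure can be left to the SAP; with 84 patients and about 20% dropout, an unstructured matrix over eight visits (8 × 9/2 = 36 parameters) may not converge and is not needed for this correction.
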